### Data Analysis

Microsoft Excel and Google Forms will be used to capture raw quantitative data and to execute the descriptive statistics in the form of percentages and frequencies. Descriptive statistics, including percentages, means, and standard deviations will be calculated for participants’ survey responses. For the pre- and posttest analysis, a paired 2-tailed *t* test analysis for the questions that assess medical knowledge will be performed. The means of both the pre and posttests will be calculated. The pretest will act as the control, and therefore, *P* values will be determined to identify if the results are statistically significant. This analysis will enable the observation of whether the podcasts were an effective intervention tool by examining a higher posttest mean score. Significance will be defined as *P*<.05.

This is an international feasibility study, and it would be of great interest to analyze participants’ country of residence in conjunction with the level of knowledge and awareness gained from the podcast to give us an insight into which country would benefit most from this form of audio learning. To conduct this, we will perform a subgroup analysis in SPSS. Furthermore, men and women have been shown to learn differently, with women preferentially being auditory learners [29]. Therefore, a subgroup analysis on gender will be carried out on SPSS. This research will help to clarify whether podcasting is a useful educational resource that is of benefit to both sexes as an alternative source of learning [30].

For this study, we only have 1 open-ended question, which is “Do you have any further comments on the podcast (duration or formatting), questions asked, or recommendations for future podcasts?” We will conduct a thematic analysis of the responses to open-ended questions [31]. To analyze and describe the comments, a coding frame will be developed. If responses contain 2 or more different statements, these statements or sentences will be coded separately or line by line.

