## Methods

### Research Design

This pre- and postpodcast intervention is a feasibility study. Feasibility studies facilitate researchers’ evaluation of whether an intervention is suitable to undergo additional investigation or whether the concepts and conclusions can be applicable and sustainable to the population [25]. A feasibility method was chosen for this study due to the lack of previously published studies on this specific intervention.

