### Type of Study and Setting

This study mainly involves quantitative data, but qualitative data will be synthesized for the 1 open-ended question on the survey tool. These questionnaires will be created and managed using Google Forms, as it is compliant with the General Data Protection Regulation. Microsoft Excel will be used to capture qualitative and quantitative data and to execute descriptive statistics in the form of percentages and frequencies [26]. This study will be carried out from March 2023 until March 2024.

The selected podcast topics revolve around global health concerns that exhibit significant variations in understanding and practices across different countries. This is intended to enable in-depth podcast discussions and survey questions that can yield insights into how nursing students use the podcasts. These podcast topics have been chosen to encompass a diversity of health-related topics affecting both high- and low-income countries.

To date, the recordings of the podcasts have been conducted. Video and audio files for 2 out of the 6 podcasts will be available for the study participants. Despite only 2 podcasts being chosen for research purposes, all 6 podcasts will be disseminated on platforms including but not limited to YouTube and Spotify. The podcasts’ duration ranges from approximately 30 to 60 minutes each. Each podcast discusses the risk factors, symptoms, and treatment or management of the global health topic.

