### Measurement Tools

For the gestational diabetes podcast, a 5-item “Yes-No-I don’t know” awareness questionnaire and a 27-item “Yes-No-I don’t know” knowledge questionnaire were developed by the researchers. For the mental health podcast, a 4-item “Yes-No-I don’t Know” awareness questionnaire and a 26-item “Yes-No-I don’t know” knowledge questionnaire were developed by the researchers. The gestational diabetes podcast has 1 additional survey question on awareness and knowledge compared to the mental health podcast, as the podcast discussion on gestational diabetes covered additional items beyond those initially prepared in the semistructured podcast guide.

The knowledge questionnaires for each of these podcasts will address 3 key themes: risk factors, symptoms, and services or treatments. Examples of the questions asked can be found in Table 1.

The only qualitative question asked at the end of each podcast is the following:

“Do you have any further comments on the podcast (duration or formatting), questions asked, or recommendations for future podcasts?”

**Table 1 table1:** Example of questions asked on knowledge and awareness.

Topic	Area being assessed	Examples of question asked before and after the podcast
Gestational diabetes	Knowledge	Is obesity or BMI a risk factor for gestational diabetes mellitus?
Gestational diabetes	Awareness	Have you heard of metformin?
Mental health	Knowledge	Is a history of mental illness in a blood relative family member a risk factors for mental illness?
Mental health	Awareness	Are you aware of risk factors for mental health problems?

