### Sampling and Sample Sizes

The sample will consist of a cohort of undergraduate nursing students from University College Cork (UCC) and the University of Galway (Ireland), the University of Fort Hare (South Africa), and Mzuzu University (Malawi). These students will be recruited through invitation via the university they are attending. Entry into the study will be entirely voluntary.

The main aim is to compare the pre- and postpodcast scores on knowledge and awareness differences with a paired 2-tailed *t* test. The inputs that will be used are the expected mean (SD) of the paired differences. As this is a feasibility study, a formal sample size calculation is not required [28].

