### Data Collection and Management

Questionnaires will be made using Google Forms, which are stored on UCC’s Microsoft OneDrive. The questionnaires will include closed-ended questions using a point scale, with points given to the tick-the-box answers of “Yes”, “No,” or “I don’t know.” These questionnaires will be distributed to UCC (Ireland), University of Galway (Ireland), University of Fort Hare (South Africa), and Mzuzu University (Malawi). Regarding the data collection, the investigators will not seek names or emails from the participants, and the data will be fully anonymized. Fully anonymized data are achievable in this study, as participants are not required to complete two different surveys. The pre- and postpodcast questions are on a single Google Form, separated only by the embedded podcast file (not 2 separate survey forms), allowing a direct comparison of survey responses without requiring participant contact details. Once the survey is submitted, the option to withdraw will no longer be available. Answers to our survey (questionnaires) will be stored on UCC-supplied Google Forms and uploaded to OneDrive. Data on knowledge and awareness will be collected from both pre- and postpodcast surveys. Information on gender, age, year of study, and the university the student is attending will also be stored, along with the consent forms. The UCC-supplied OneDrive will also be used during data collection and data analyses due to the ability to store data generated on the cloud automatically. Data will be stored for a minimum of 10 years. The data will be controlled by the UCC study members. General Data Protection Regulation will be observed at all times with all information anonymized.

Data collection tools will be structured according to the research themes outlined as follows:

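### The pretest is a baseline, not a control: a significantly higher posttest mean shows that scores changed, not that the podcast changed them

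*Protocol article*

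**What the plan says.** All references are to the protocol article.

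- **Design.** Research Design: "This pre- and postpodcast intervention is a feasibility study". One group is described, and each student is compared with himself or herself.
- **Items and timing.** In Measurement Tools, the column heading of Table 1 reads "Examples of question asked before and after the podcast". Data Collection and Management adds: "The pre- and postpodcast questions are on a single Google Form, separated only by the embedded podcast file". Type of Study and Setting gives the gap: "The podcasts’ duration ranges from approximately 30 to 60 minutes each".
- **Test.** Sampling and Sample Sizes: "The main aim is to compare the pre- and postpodcast scores on knowledge and awareness differences with a paired 2-tailed" t test. Data Analysis sets significance at P<.05.
- **Inference.** Data Analysis states "The pretest will act as the control", presents the P values as following from that, and says the analysis will show "whether the podcasts were an effective intervention tool by examining a higher posttest mean score".
- **Use of the result.** Type of Study and Setting says that the completed study will determine whether podcasting is effective for knowledge and awareness. Positive results lead to a broader survey and the release of more podcasts.
- **Limitations.** Strengths and Limitations names nonresponse, selection bias and generalisability. It does not name the absence of a comparator, retest effects or the immediate-only posttest.

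**The concern.** A control shows what would have happened without the intervention. A pretest shows only where the student started. If scores would have risen at the second asking for other reasons, the pretest cannot reveal it, and the planned reading credits the whole rise to the podcast.

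Three features make this concrete here.

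1. **Repeat exposure.** The article defines awareness as having heard of a term or topic, and one example item asks whether the student has heard of metformin. Reading that item at the pretest can by itself make Yes a true answer at the posttest.
2. **Scoring.** For awareness items and for the prompted symptom items, Yes scores 1, and No or I don't know scores 0. Any general drift toward Yes therefore counts as gain.
3. **Expectation.** Students know that they have just received an educational intervention and are being asked the same questions again.

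At stake is the study's main conclusion, and with it the decision on follow-on work.

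**Working it through.** **1. What the paired test estimates.** Let D be a student's posttest score minus pretest score. Then

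E(D) = podcast effect + shift from repeat testing, Yes-drift and expectation.

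The test statistic is t = mean(D) / (SD(D)/√n) on n − 1 degrees of freedom. It tests E(D) = 0. One group gives one equation with two unknown terms, so a small P value cannot show which term is nonzero. This step needs no numerical assumption.

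**2. Is there a figure to reproduce?** No. The article gives no sample size, expected change or SD, and says that a feasibility study needs no formal calculation. The only total available is the student pool, 850 + 450 + 719 + 376 = 2395, which adds up.

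**3. Illustration.** Suppose the podcast adds nothing and the mean score still rises by g items. The chance of a significant rise is

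P = 1 − F(t₀.₉₇₅,ₙ₋₁; n − 1, λ), with λ = (g/SD)·√n,

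where F is the noncentral t distribution function.

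Inputs:
- 2-sided alpha 0.05, from the article.
- n = 120 and 240, assumed. These are about 5% and 10% of 2395 (120/2395 = 0.050; 240/2395 = 0.100).
- g = 1 and 0.5 items, assumed. On the 27-item gestational diabetes knowledge score, 1/27 = 3.7%.
- SD of change 3 to 6 items, assumed.

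Worked case: g = 1, SD = 4, n = 120. Then λ = 0.25 × √120 = 2.74, the critical value is 1.98, and P = 0.78. With n = 240, λ = 0.25 × √240 = 3.87 and P = 0.97.

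| Gain unrelated to the podcast | SD of change | n = 120 | n = 240 |
|---|---|---|---|
| 1 item | 3 | 0.95 | 0.999 |
| 1 item | 4 | 0.78 | 0.97 |
| 1 item | 6 | 0.44 | 0.73 |
| 0.5 item | 3 | 0.44 | 0.73 |
| 0.5 item | 4 | 0.27 | 0.49 |
| 0.5 item | 6 | 0.15 | 0.25 |

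With no such shift (g = 0), the chance of a significant rise is the nominal 0.025.

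**4. What the table shows.** A small shift can be enough for significance at plausible response numbers, and more responders make this more likely. It does not show that such a shift exists.

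**The case against.** The strongest case for the plan is that this is a voluntary feasibility study with limited resources, for which a single-group pre-post design is a legitimate choice. Other sections hedge: the Conclusions speak of potential utility, and Expected Findings says only that the results could illuminate the question. The follow-on is further research. This stands as a defence of the design. It does not cover the inference rule in Data Analysis or the statement in Type of Study and Setting that effectiveness will be determined.

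Further points on that side, and what remains of each:

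- **A reader might infer that a podcast that teaches nothing would be declared effective.** The documents do not support that. It requires an upward shift large enough to matter, and they give no size for one. They describe no feedback on correct answers between the two tests, so an upward shift on knowledge items is an assumption. The supportable statement is that a rise could come from elsewhere and the plan cannot tell.
- **A reader might picture the same items answered again minutes later in one sitting.** The gap is at least a podcast of about 30 to 60 minutes if it is heard in full. A single sitting is a fair inference from the single form but is not stated.
- **Cueing by the pretest is not a gain without the podcast.** A student who listens for the tested answers still gets them from the podcast. Cueing limits how far the result applies to listeners who take no pretest; it should not be counted as a rival to the podcast effect.
- **The clearest mechanism concerns awareness, while Data Analysis names the t test only for medical knowledge questions.** This is true of that section. Sampling and Sample Sizes, however, puts awareness within the main paired comparison, and the third research question asks about effectiveness for awareness.

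**Conclusion.** The concern holds as a fault of inference. The paired t test is sound for within-student change. Calling the pretest a control, and reading a significantly higher posttest mean as effectiveness, goes beyond what one group answering the same items twice can show. That conclusion follows from the design alone.

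Its size cannot be fixed from the documents. Under the assumed inputs, a 1-item gain unrelated to the podcast would be significant with probability 0.95 to 0.44 at n = 120 and 0.999 to 0.73 at n = 240. For a 0.5-item gain the ranges are 0.44 to 0.15 and 0.73 to 0.25. These rest on assumed gain, SD and number of responders, and no single cell should be quoted as the expected error rate.

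The change should be made, because the effectiveness statement also drives the decision on further work and the limitations give the reader no warning.

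**What to change.** Change wording only:

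1. **Data Analysis.** Replace control with baseline. Replace the effectiveness inference with a statement such as: *the analysis estimates uncontrolled immediate pre-post change; retest and expectation effects are not excluded.*
2. **Type of Study and Setting.** Limit the statement that the study will determine effectiveness in the same way, so that the decision on follow-on work rests on an observed immediate change and not on a demonstrated podcast effect.
3. **Strengths and Limitations.** Add the missing comparator, retest effects (with the have-you-heard-of items as the clearest case) and immediate-only measurement.

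This needs no new data and no change to the questionnaires, so it can be made while data collection continues. The cost is a weaker claim.

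Adding items from the other topic as an internal control is not recommended at this stage. It would not remove cueing or topic-specific expectation. Students who complete both forms could contaminate it, and anonymous responses cannot be linked to detect them. It would also create two versions of the instrument partway through data collection.

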### Objective of the Feasibility Study

This paper explores the impact of health-related podcasts as an intervention tool to support the knowledge and awareness of nursing students on a given topic. To address this objective, we aim to answer the following questions:

Can podcasts support listeners' knowledge of global health topics?Is knowledge attainment from podcasts different across Ireland, South Africa, and Malawi?Is podcasting effective for supporting awareness in nursing students on global health diseases and issues?

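### The plan asks whether knowledge gain differs between countries, but the only test it names is a within-person pre/post t test, so no stated method compares countries

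*Protocol article*

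**What the plan says.** The Objective section lists as its second question: "Is knowledge attainment from podcasts different across Ireland, South Africa, and Malawi". The Data Analysis section returns to it, saying that country will be examined alongside the knowledge and awareness gained, to "give us an insight into which country would benefit most from this form of audio learning". The method follows in one sentence: "To conduct this, we will perform a subgroup analysis in SPSS". Gender is handled the same way.

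The inferential method that is spelled out is a within-person one. Sampling and Sample Sizes gives the main aim as to "compare the pre- and postpodcast scores on knowledge and awareness differences with a paired 2-tailed *t* test". Data Analysis says that "a paired 2-tailed *t* test analysis for the questions that assess medical knowledge will be performed", sets the threshold ("Significance will be defined as *P*<.05"), and adds that this will show "whether the podcasts were an effective intervention tool by examining a higher posttest mean score". No between-country or between-gender test, interaction term or model of the gain is named.

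The variables for such a comparison are collected: "Information on gender, age, year of study, and the university the student is attending will also be stored".

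**The concern.** A paired t test in one country asks whether that country's mean gain is zero. The research question asks whether the mean gains of three countries are equal. Answering the first three times does not answer the second, because significant in one country and not in another is not evidence of a difference between them. The P value depends on the number of respondents as well as on the gain, and the student populations differ 3.5-fold.

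International comparison is what the Discussion presents as new about this study. If the country analysis is a set of within-country verdicts, a country could be said to benefit more, or not to benefit, when the podcast worked equally well in all three.

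**Working it through.** **The plan's own figure.** The Abstract gives 850 (Cork), 450 (Galway), 719 (Malawi) and 376 (South Africa). 850 + 450 + 719 + 376 = 2395, which matches the stated total. By country this is 1300, 719 and 376, and 1300/376 = 3.5. These are student populations, not expected respondents.

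**Inputs not in the document (assumptions).** The article gives no response rate, effect size or SD. I assume the same true gain d in every country, in units of the SD of the paired difference, and the same response rate in every country. Both d and the response rate are varied.

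**Formula.** The power of the two-sided 0.05 paired t test in a country with n respondents comes from the noncentral t distribution with n − 1 degrees of freedom and noncentrality d√n. With powers p1, p2 and p3,

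P(some but not all significant) = 1 − p1·p2·p3 − (1 − p1)(1 − p2)(1 − p3).

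**Worked case: 10% response, d = 0.3.** n = 130, 72 and 38, so power is 0.924 (Ireland), 0.709 (Malawi) and 0.437 (South Africa).
- All significant: 0.924 × 0.709 × 0.437 = 0.286.
- None significant: 0.076 × 0.291 × 0.563 = 0.012.
- Mixed verdicts: 1 − 0.286 − 0.012 = 0.70.

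The gain is identical by construction, so the gap between 92% and 44% comes from sample size alone.

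**Range of the mixed-verdict probability.**

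| Response (n Ireland/Malawi/South Africa) | d = 0.2 | d = 0.3 | d = 0.5 |
|---|---|---|---|
| 5% (65/36/19) | 55% | 78% | 56% |
| 10% (130/72/38) | 77% | 70% | 16% |
| 20% (260/144/75) | 74% | 31% | 1% |
| 100% (1300/719/376) | 3% | about 0% | about 0% |

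At d = 0.7 it is 19% at 5% response and about 1% at 10% response.

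**Large gains.** Where the probability is near zero, it is because every country is significant. Three significant tests do not say which country gained more.

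**A direct comparison under the same conditions.** A one-way ANOVA on individual gains, with d = 0.3 in all countries (10,000 simulated studies per case), declares a country difference in 4.9%, 5.2% and 5.2% of studies at 5%, 10% and 20% response. That is the nominal 5%.

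**Gender.** The split is not in the document. Assuming 240 respondents with 216 women and 24 men, power at d = 0.3 is 0.992 and 0.291, and the chance that exactly one sex is significant is 0.992 × 0.709 + 0.291 × 0.008 = 0.71. At d = 0.5 it is 0.35.

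**Scale.** Suppose students in two countries each learn 40% of the items that they did not know (illustrative). From a 50% baseline the score rises to 70%, and from 80% to 88%. On 27 items the raw gains are 0.4 × 27 × 0.5 = 5.4 and 0.4 × 27 × 0.2 = 2.2. The odds ratios are (0.70/0.30)/(0.50/0.50) = 2.33 and (0.88/0.12)/(0.80/0.20) = 1.83. Equal learning in this sense looks unequal on both scales, so a logistic model does not remove the dependence on baseline.

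**The case against.** The article never says that the subgroup analysis is a paired t test run separately in each country. A reader might infer that, since no other test is named, but the text does not establish it. The sentence on country ties residence to the amount gained, which would fit a between-country comparison of gains in SPSS. The article is condensed, and models and covariates are commonly left to a fuller document. This stands, and it is why the numbers above are conditional.

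It does not dispose of the point. The article does fix its test, sidedness, threshold and criterion of effectiveness, and that analysis cannot answer its second research question. On the other reading, the question has no stated method.

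A reader might also infer that the plan will produce false country and gender differences. That is not supported: the risk depends on response and effect size, neither of which is given, and at gains of 0.5 SD or more with moderate response it is small.

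For gender, the stated aim is whether both sexes benefit. That is partly a within-group question, which estimates by sex can answer. Only the rationale, that men and women learn differently, is a between-group claim. Nor does the document support reading collection of year of study without a stated role as an error in itself: the Conclusions give listener demographics a descriptive purpose.

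Finally, this is a feasibility study and the country analysis is worded as an insight. That argues for a simple model and modest claims. It does not excuse a test that does not match the question.

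**Conclusion.** The point holds in a conditional form. The article poses a between-country question and names no between-country comparison. If the undefined subgroup analysis means repeating the paired test by country, it does not compare countries. With equal true gains and equal response rates (both assumed), the chance of mixed verdicts runs from about 0% to about 80%. It is highest with small to moderate gains and low response, and at the low end the separate tests are uninformative instead of misleading. The criticism is weaker for gender and applies only to a claim that the sexes differ; the gender figures also rest on an assumed 90:10 split.

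**What to change.** In Data Analysis, replace the subgroup analysis for country with one direct comparison of the knowledge gain between countries for each topic. Either a time-by-country interaction, or a model of the post score on country adjusted for pre score and year of study, would do. Choose one in advance, because the two can differ when baselines differ. Report the country differences with 95% confidence intervals, and state that no country difference will be inferred from separate within-country P values. Show baseline scores by country beside the contrast and name the scale used, since raw gains and odds ratios both depend on baseline.

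For gender, report the gain with a 95% confidence interval in each sex to address benefit in both, and use a time-by-gender test for any claim that men and women differ. A full set of time interactions with age, year and gender is more than a feasibility study needs.

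The cost is a little more analysis in SPSS, which is already planned, with variables already collected, and more cautious statements about countries.
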